### Pedometers

Pedometers will be used to assess adherence to the walking intervention and objectively compare the amount walked by people in the intervention group with that walked in the control group. However, they are also an inexpensive and effective intervention to increase levels of physical activity [17]. In order to control for the impact of pedometers on walking behavior, only half of the participants in the intervention and control groups will be randomly allocated with pedometers. This is because wearing a pedometer might increase participants walking regardless of whether they are in the intervention or control group. They will be asked to wear them for seven consecutive days at each assessment point (baseline pedometer data will be provided once the research team has received a signed consent form) and to complete a form recording how many steps they took over the 7-day period.

### Primary outcome

The primary outcomes are whether participants find the study and intervention acceptable and whether a full randomized controlled trial is warranted and feasible.

### Secondary outcomes

The secondary outcomes are the refinement of the walking intervention based on views from participants and stakeholders and estimates of key aspects of trial design needed to design a full-scale randomized trial design, if warranted, including the following:The number of eligible participants, recruitment and retention rate, and response rates to initial and follow-up questionnairesThe utility of the objective (pedometer) and subjective (self-report) methods to assess adherence to the walking interventionEstimates of the variability of the QoL

### Sample size

For the feasibility trial, we aim to consecutively recruit a minimum of 30 patients with recurrent or metastatic cancer to both the control and intervention groups (60 patients in total). A sample size of 30 per arm will be sufficient to estimate the standard deviation of our QoL outcomes and allow estimation of the true treatment difference. The latter is needed to perform a power calculation for the main study. A definitive sample size of a large-scale RCT will be determined from the results of this trial.

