**Conclusions:**

Data from this study will be used to refine the walking intervention, investigate the acceptability of the intervention and study design, and determine the most appropriate outcome measures thereby providing estimates of the factors needed to design the main study.

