Here, we describe the protocol of the CanWalk study, which aims to assess the feasibility and acceptability of undertaking a randomized controlled trial of a community-based walking program to enhance quality of life in people with recurrent or metastatic cancer. The study will promote a walking intervention, assess whether participants find it acceptable and evaluate whether a full randomized controlled trial is warranted and feasible. Specific objectives include:The development of the walking intervention to encourage intervention uptake [13];To investigate the acceptability to participants of a) the walking intervention, b) the study materials, and c) being randomized to intervention or control; and to assess d) the acceptability and timing of the selected outcome measures, and e) use of pedometers to enhance and measure adherence;To provide estimates of key aspects of trial design needed to design a full-scale randomized trial design, if warranted, including; a) number of eligible participants, b) recruitment rate, c) retention rate, d) response rates to initial and follow up questionnaires, e) the utility of objective and subjective methods to assess adherence to the walking intervention, and 4) generation of an estimate of the variability in quality of life.

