## Methods

### Design

This is a mixed methods [14] feasibility study based on an exploratory two-center randomized controlled trial (RCT) with nested qualitative interviews. The study is registered with the International Standard Randomized Control Trial Number Register (ISRCTN42072606). Participants will be randomized, using a central online system, 1:1 between the walking intervention and standard care using minimization (based on age, sex, and physical activity levels).

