## Discussion

This study will explore the feasibility and acceptability of a community-based walking program in enhancing QoL outcomes in people with recurrent or metastatic cancer. To date, this is the first study investigating whether a brief walking intervention on its own is sufficient to enhance the health and well-being of these people. This is particularly important because although the number of people living with cancer continues to increase [2] people with recurrent or metastatic disease report reduced QoL [1].

Despite being the first of its kind, the intervention will only be available in English and therefore the uptake/views of minority ethnic groups may be underrepresented. Also, eight tumor types are included in the trial sample, which means that findings cannot be generalized to all tumor groups.

Findings from this study will determine whether recruitment to a full-scale trial is feasible and provide initial data for future sample size calculations. It will collect information on the acceptability of the walking intervention and permit refinement where necessary. Furthermore, the study will assess whether the outcomes being used are acceptable, appropriate and sensitive to change in this population. Finally, the study will investigate the acceptability of the use of pedometers and their influence on walking behavior.

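### Thirty per arm cannot fix the treatment difference closely enough to power the main trial, yet the Sample size section makes that estimate the power input

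*Protocol article*

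**What the plan says.** The Sample size section sets a minimum of 30 recruited patients per arm, 60 in all. It gives two reasons for that number. The first concerns variability: "A sample size of 30 per arm will be sufficient to estimate the standard deviation of our QoL outcomes". The second is that the number will "allow estimation of the true treatment difference. The latter is needed to perform a power calculation for the main study". Grammatically, the quantity called necessary for the power calculation is the treatment difference, not the SD. The section closes: "A definitive sample size of a large-scale RCT will be determined from the results of this trial". It states no precision target, minimally important difference, significance level, power or assumed effect.

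The objectives at the end of the Background list what is needed to design the main trial: eligible numbers, recruitment, retention, response rates, the utility of the adherence measures, and "generation of an estimate of the variability in quality of life". The Secondary outcomes section repeats that list. Neither mentions a treatment difference. The Data management and analysis section plans 95% confidence intervals for QoL measures and independent t-tests between groups.

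**The concern.** A sample that is large enough to estimate an SD is usually far too small to estimate a difference between two means. The plan treats the two tasks as if the same 60 patients served both, and then passes the weaker estimate to the main trial.

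The required sample size varies with the inverse square of the assumed difference, so error in that difference is magnified. A difference that is too large by chance gives an underpowered main trial. One that is too small by chance gives a needlessly large trial. A zero or negative one gives no usable sample size. The plan states this method outright, so it is not a detail left to a fuller document.

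**Working it through.** **Inputs from the protocol article.** n = 30 per arm (Sample size); allocation "1:1 between the walking intervention and standard care using minimization" (Design); comparison by independent t-test (Data management and analysis). The 30 per arm comes with no formula, so there is no calculation of the plan's own to reproduce. The check is what 30 per arm delivers, in SD units.

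**Assumptions not in the documents.** Main trial at two-sided 5% with 90% power; true effect 0.3 SD, varied from 0.2 to 0.5; retention of 100% or, as a variant, 80%. Step 1, at full follow-up, needs none of these.

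**1. Precision at 30 per arm, all observed**
- Standard error of the difference = √(2/30) = 0.258 SD.
- 95% half-width = t(0.975, 58 df) × 0.258 = 2.002 × 0.258 = 0.52 SD. With 24 per arm (20% loss) it is 0.58 SD.
- SD: chi-square limits on 58 df give 0.847 to 1.222 times the estimate.
- For comparison, a half-width of 0.2 SD would need 2 × (1.96/0.2)² = 192.1, so 193 per arm.

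**2. Correct main-trial size at a true 0.3 SD**
- n per arm = 2 × (1.960 + 1.282)² / 0.3² ≈ 233.5, rounded up to 234.

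**3. Sizing on the observed difference** (400,000 simulated feasibility studies per scenario; each main trial is sized on the observed difference and SD; true power = Φ(d/√(2/N) − 1.960))

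| True effect, n per arm | Difference ≤ 0 | Correct N per arm | Middle half of planned N* | Mean true power* | Power < 80%* |
|---|---|---|---|---|---|
| 0.2 SD, 30 | 22% | 526 | 117 to 1,000 | 64% | 58% |
| 0.3 SD, 30 | 12% | 234 | 83 to 552 | 73% | 49% |
| 0.5 SD, 30 | 3% | 85 | 45 to 180 | 81% | 39% |
| 0.3 SD, 24 | 15% | 234 | 73 to 531 | 71% | 51% |

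*Among studies with a positive observed difference.

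To see one case by hand, take the lower quartile of 83 per arm at a true 0.3 SD. Then √(2/83) = 0.155, 0.3/0.155 = 1.93, and Φ(1.93 − 1.96) is about 49%, where 90% was intended. At 0.3 SD with 30 per arm, only 12% of all simulated studies lead to a size within 25% of the correct one.

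**4. Sizing on the SD alone, target difference fixed separately**
- Planned N lies within 0.67 to 1.39 times the correct N (95% range).
- Mean true power is about 89%, and about 8% of main trials fall below 80%.

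**The case against.** The best defence has four parts.

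- **The text claims only that the difference can be estimated, and confidence intervals are promised.** An unbiased estimate can indeed be computed, and the intervals would show how wide it is. But they do not alter the use that the Sample size section gives to the estimate.
- **Acceptability and feasibility are the primary outcomes.** This stands. A reader might infer that the study exists to supply the treatment difference, but the Primary outcome and Secondary outcomes sections show otherwise. The fault is confined to the Sample size section, which goes further than the study's own objectives.
- **No inflation for dropout is not an error here.** This stands too. Retention is one of the quantities to be estimated, and 30 per arm is a minimum. The loss figures above only show sensitivity.
- **Recruitment has closed, and the main trial's protocol must justify its own size.** Both are fair. The fault does not touch this trial's participants, allocation or primary outcomes, but the stated method still governs a trial that has not been sized.

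Two stronger readings are tempting and unsupported. One is that the main-trial outcome will be whichever of the eight repeated scales shows the largest between-arm difference. The Discussion says that "the study will assess whether the outcomes being used are acceptable, appropriate and sensitive to change in this population", and the abstract's conclusions speak of choosing outcome measures. Neither states a selection rule based on between-arm differences; sensitivity to change can mean change within patients, for which paired tests are planned. Most of the eight scales are not QoL measures in any case. The other is that a low estimate would stop the main trial. No section makes progression depend on the observed difference.

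**Conclusion.** The point holds, limited to the Sample size section. The SD justification for 30 per arm is sound and should stay. The claim about the treatment difference should not: a half-width of 0.52 SD follows from 30 per arm alone and is too wide for a design effect.

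The consequences for the main trial depend on the assumed effect and power. At 0.3 SD and 90% power, following the plan as written has about even odds of a main trial below 80% power, given a positive estimate. Over 0.2 to 0.5 SD those odds run from 58% to 39%. Mis-sizing is therefore likely but not certain: with 30 per arm, between about 8% and 20% of feasibility studies would land within 25% of the correct size.

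**What to change.** Delete the claim that the estimated difference is needed for the power calculation, and align the Sample size section with the objectives and secondary outcomes. Suggested wording:

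> Thirty per arm is chosen to estimate the SD of the QoL outcomes (95% confidence interval about 0.85 to 1.22 times the estimate, before attrition). The between-arm difference will be reported with its 95% confidence interval and will not be used as the effect size for the main trial. The main trial will be powered on a separately justified minimally important difference, using the SD from this study, with allowance for its uncertainty, and the attrition observed.

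The allowance could be an upper confidence limit for the SD; the one-sided 80% limit, 1.09 times the estimate on 58 df, is one convention among several.

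**Cost.** No extra patients and no change to this study's conduct. Someone must find and defend a minimally important difference, because the article gives none. Allowing for uncertainty in the SD also enlarges the main trial: by about 19% with the 80% limit (1.09² = 1.19).

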### Data management and analysis

All quantitative data will be double entered and subjected to basic descriptive statistical tests, including calculation of means and frequencies; 95% confidence intervals will be presented to display the imprecision in QoL measures. Independent *t*-tests and χ^2^ tests will be used for two-group measure comparisons. Their paired equivalents will be used to analyze changes in outcome measures between baseline and follow-up. Rates for process measures (for example, recruitment, attrition) will be calculated.

Reasons for non-participation and attrition will be collected to inform future recruitment and retention strategies. We will also collect data on age and gender, with consent, from all eligible people, regardless of whether they choose to participate or not, to explore whether participation rate varies according to these variables.

Audio recordings of interviews will be transcribed verbatim and analyzed using framework analysis; a widely used matrix-based method for collating, reviewing, and understanding qualitative data [26]. All data will be stored securely, and raw data will only be accessible to the study chief investigator (JA) and researchers (JH, VT).

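### The planned unadjusted t-tests ignore the pre-randomisation score and the minimisation factors, so they waste precision in the treatment difference that is meant to inform the main trial

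*Protocol article*

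**What the plan says.** The Data management and analysis section of the protocol article names the methods, with independent t-tests and chi-square tests between the arms and paired tests over time: "tests will be used for two-group measure comparisons. Their paired equivalents will be used to analyze changes in outcome measures between baseline and follow-up". It adds that "95% confidence intervals will be presented to display the imprecision in QoL measures". No covariate is mentioned.

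Other sections show what is available for adjustment:

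- **Design:** randomisation is "1:1 between the walking intervention and standard care using minimization (based on age, sex, and physical activity levels").
- **Assessments, Table 2:** the eight scored instruments are completed at T0, T1, T2 and T3. The footnote states that randomisation follows return of the baseline questionnaire.
- **Sample size:** the target is "a minimum of 30 patients with recurrent or metastatic cancer to both the control and intervention groups (60 patients in total"). This number is justified by estimating the SD of the quality-of-life outcomes and the true treatment difference, and the difference is said to be needed for the power calculation of the main study.

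**The concern.** A score taken before randomisation on the same instrument is a legitimate covariate and usually the strongest one available. The named t-test does not use it. Nor does it use the three factors that the allocation deliberately balances. The method is stated in the protocol, so it would have to be replaced rather than merely filled in by a later analysis plan.

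What is at stake is the precision of the between-arm difference. Acceptability and feasibility are the primary outcomes, so no efficacy claim depends on these tests. But the difference and its variability are meant to feed the design of the next trial, and 30 per arm leaves little precision to spare.

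A second, smaller issue is that change from baseline is analysed only by paired tests. These describe change over time, which in advanced cancer can reflect disease course, concurrent treatment or regression to the mean. No between-arm contrast of change is named beside them.

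**Working it through.** **Inputs from the protocol.** At least 30 per arm, 1:1 allocation, 95% intervals, minimisation on age, sex and physical activity, and baseline measured before randomisation.

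**Inputs not in the protocol.** The SD, the baseline-to-follow-up correlation r, the prognostic strength of the factors, and dropout. The SD is set to 1, so results are in SD units; r is varied. The 30 per arm cannot be reproduced, because no target difference, SD, power or precision is given.

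**1. Between-arm half-width**

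- Unadjusted: t(0.975, 58) × √(2/30) = 2.0017 × 0.2582 = 0.517.
- ANCOVA on baseline only: t(0.975, 57) × √[(2/30)(1 − r²)(1 + 1/56)]. The last factor is the cost of estimating the slope. At r = 0.5: 2.0025 × 0.2582 × 0.8660 × 1.0089 = 0.452.
- Unadjusted t-test on change scores, the other possible reading of the protocol's sentence: 2.0017 × √[(2/30) × 2(1 − r)].

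| r (assumed) | t-test, follow-up score | t-test, change score | ANCOVA on baseline | follow-up t-test ÷ ANCOVA |
|---|---|---|---|---|
| 0 | 0.517 | 0.731 | 0.522 | 0.99 |
| 0.1 | 0.517 | 0.693 | 0.519 | 1.00 |
| 0.3 | 0.517 | 0.612 | 0.498 | 1.04 |
| 0.5 | 0.517 | 0.517 | 0.452 | 1.14 |
| 0.7 | 0.517 | 0.400 | 0.373 | 1.39 |

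**2. Price of more covariates.** With q covariate degrees of freedom that add nothing beyond baseline, and without crediting the balance that minimisation provides, the slope factor becomes 1 + q/(57 − q) and the t quantile has 58 − q degrees of freedom.

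- q = 4 (baseline, age, sex, two-level activity): factor 1 + 4/53 = 1.0755, t = 2.0049. Half-widths are 0.534, 0.512, 0.465 and 0.383 at r = 0.1, 0.3, 0.5 and 0.7.
- q = 7 (four-level activity, plus centre): factor 1 + 7/50 = 1.14, t = 2.0076. Half-widths are 0.528, 0.479 and 0.395 at r = 0.3, 0.5 and 0.7. At r = 0.3 this is slightly worse than the t-test.

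**3. Type I error after minimisation.** Trials of 60 patients were simulated, minimised on three assumed binary factors with an 80% biased coin (3,000 runs per setting).

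| r | Unadjusted t-test: type I error | Adjusted: type I error | Mean SE, unadjusted | Mean SE, adjusted |
|---|---|---|---|---|
| 0.5 | 4.8% to 5.0% | 5.0% to 5.4% | 0.257 to 0.258 | 0.226 |
| 0.7 | 4.0% to 4.3% | 4.7% to 5.2% | 0.257 to 0.258 | 0.186 |

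The simulation standard error near 5% is √(0.05 × 0.95/3000) = 0.4 percentage points. The unadjusted test is therefore valid to slightly conservative, and most of the gain comes from the baseline score.

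**4. Paired tests.** With no treatment effect and the same drift of 0.2 to 0.4 SD in both arms (assumed; 20,000 runs), separate paired tests gave significance in exactly one arm in 30% to 49% of trials at r = 0.5, and in 34% to 50% at r = 0.7. The between-arm t-test stayed near 5%. This shows only why paired tests cannot stand in for a comparison of the arms.

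**The case against.** The strongest reply is that this is a feasibility trial: an unadjusted comparison is unbiased, any estimate at this size is imprecise, and the size of the gain rests on a correlation the protocol does not give. All of that stands. It limits the weight of the point, but does not justify discarding a baseline score already in hand.

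The planned 95% intervals may be meant for descriptive means rather than for the difference between arms. The wording allows this, so it cannot be said that a stated interval for the difference is too wide. The loss concerns the difference itself, which the Sample size section says will be estimated.

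A reader might infer more than the documents support:

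- *That the t-test is invalid or biased by chance baseline imbalance.* Its SE already includes that imbalance, and the simulation shows at most mild conservatism.
- *That the plan intends to read before-after change as treatment effect.* Nothing says that the paired tests are run by arm, compared across arms or taken as effect. The two-group comparison has its own sentence.
- *That the correlation needed to size the main trial is lost.* It can be recovered from the SDs of baseline, follow-up and change, since s_change² = s₀² + s₁² − 2r·s₀·s₁. The protocol just does not plan to report it.

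**Conclusion.** The point holds as an avoidable loss of precision. The t-test on follow-up scores gives a half-width about 4%, 14% or 39% larger than baseline-adjusted ANCOVA at r = 0.3, 0.5 or 0.7. There is no gain at r of 0.1 or below. Adding the minimisation factors with few degrees of freedom keeps most of the benefit at moderate correlations, but at r = 0.3 it leaves almost none (0.512 against 0.517) if those factors carry no further information. Reading the planned t-test as one on change scores does not rescue it, because ANCOVA is narrower at every correlation tabulated.

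These figures assume 30 per arm with complete follow-up, a common SD and a linear relation to baseline. The paired tests are a secondary matter of clarity. The primary outcomes are unaffected.

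**What to change.** Replace the sentence on two-group comparisons, for continuous outcomes, with wording such as:

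> For each continuous outcome, the between-arm difference at T1, T2 and T3 will be estimated by ANCOVA in the arms as randomised, adjusted for the baseline value, age, sex and baseline physical activity level, with a 95% confidence interval. The SD, residual SD and baseline-to-follow-up correlation will be reported for planning the main trial. Change within each arm will be presented descriptively and not as evidence of effect.

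Code the factors sparingly, with age linear and activity in as few levels as the minimisation allows. Centre is not listed as a minimisation factor and need not be added. The χ² comparisons of categorical measures are not affected by this change.

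All covariates are already collected, so the change is possible although recruitment has closed. It should be fixed before the outcome data are analysed. The cost is a few degrees of freedom, with a slightly wider interval if the correlation proves very low.

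### The visit-by-visit t-tests and paired tests make no use of the earlier scores of people missing at that visit, so QoL-related drop-out can bias follow-up means upward and the follow-up SD modestly downward

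*Protocol article*

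**What the plan says.** The Data management and analysis section of the protocol article fixes the tests. For group comparisons: "Independent *t*-tests and χ^2^ tests will be used for two-group measure comparisons". For change over time: "Their paired equivalents will be used to analyze changes in outcome measures between baseline and follow-up". It adds that "95% confidence intervals will be presented to display the imprecision in QoL measures". No model that joins the visits is named.

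QoL (FACT-G) is collected by post at baseline and at 6, 12 and 24 weeks (Assessments, Table 2). The footnote to Table 2 places randomization after return of the baseline form.

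The Sample size section says that 30 per arm "will be sufficient to estimate the standard deviation of our QoL outcomes" and also allows the treatment difference to be estimated. It then says: "A definitive sample size of a large-scale RCT will be determined from the results of this trial". The variability of QoL is listed under Secondary outcomes. The primary outcomes are acceptability and feasibility.

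**The concern.** A two-sample t-test at 24 weeks needs a 24-week score, and a paired test needs a baseline and a 24-week score. Someone who returns the 6- and 12-week forms and then dies, deteriorates or withdraws counts in the earlier tests but adds nothing to the 24-week result, although the earlier scores carry information about it. Each visit is therefore analysed on a different subset.

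The population has recurrent or metastatic disease, and the section itself plans to calculate attrition. It is reasonable, though not documented, to expect people whose QoL is falling to be likelier to leave. Those who remain would then have better and less variable QoL than those randomised. A follow-up SD from them, carried to the main trial, would make that trial somewhat too small.

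**Working it through.** **Inputs.** From the article: 30 per arm (60 in total), visits at baseline, 6, 12 and 24 weeks, and 95% confidence intervals. Not in the article, so assumed: the drop-out rate, its link with QoL, and the correlation between visits. The article gives no SD, effect size, power or target precision for the 30 per arm, so that figure cannot be reproduced. Only its implied precision can be computed.

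**Step 1: one-visit check.** Follow-up score Y ~ N(0, 1); probability of a missing form = expit(a − log(OR)·Y), with a set to give the stated loss. For a fixed difference to detect, the main-trial N is proportional to SD², so the shortfall is 1 − SD².

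| Loss | OR per SD lower QoL | Responder mean | Responder SD | Main-trial N short by |
|---|---|---|---|---|
| 20% | 1 | 0.00 | 1.00 | 0% |
| 20% | 2 | +0.13 | 0.967 | 1 − 0.935 = 6.5% |
| 20% | 3 | +0.19 | 0.933 | 1 − 0.871 = 13% |
| 30% | 1 | 0.00 | 1.00 | 0% |
| 30% | 2 | +0.19 | 0.958 | 1 − 0.917 = 8% |
| 30% | 3 | +0.27 | 0.916 | 1 − 0.840 = 16% |

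Two extremes: losing exactly the lowest 20% of scores gives a mean of +0.35 and an SD of 0.76. Loss concentrated in mid-range scores leaves the mean unchanged and raises the SD to 1.03 (20% loss) or 1.05 (30% loss).

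**Step 2: four visits.** 1,000,000 simulated subjects, SD 1, correlation 0.7 (compound-symmetric or AR(1)), no true change. Drop-out is monotone at 1 − 0.70^(1/3) = 11% per visit, so 70% remain at 24 weeks, with OR 2.7 per SD. The comparison is a likelihood-type estimate that uses all visits (sequential regression under missing at random).

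| Drop-out depends on | Responder mean | Responder SD | N short by | All-visit mean | All-visit SD |
|---|---|---|---|---|---|
| Previous score | +0.15 to +0.20 | 0.95 to 0.97 | 6 to 9% | 0.00 | 1.00 |
| Current score | +0.21 to +0.23 | 0.93 to 0.94 | 12 to 13% | +0.08 to +0.12 | 0.95 to 0.96 |

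At 32% loss the upper end of the mean bias is 0.24 SD. Paired change from baseline among responders was biased by only −0.06 to +0.07 SD, so the follow-up means and SDs are affected more than the paired change.

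**Step 3: sampling error of the SD.** The 95% CI for an SD runs from √(df/χ²₀.₉₇₅) to √(df/χ²₀.₀₂₅) times the estimate. Pooled over 60 people (58 df) this is 0.85 to 1.22. With 30% loss (42 people, 40 df) it is 0.82 to 1.28. Squaring the latter, 0.821² = 0.67 and 1.28² = 1.64, so the implied main-trial N runs from about 33% below to 64% above its point estimate. A 3 to 7% bias in the SD is well inside that interval.

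**The case against.** The strongest reply is that this is a condensed article. It does not say that analysis is limited to responders, and the Project management section mentions detailed plans for data management and analysis that are not shown. Rules for deaths and missing forms may stand there, so their absence is no finding. The same applies to a comparison of leavers with stayers. What remains is that the article names specific tests, and those tests cannot use earlier scores unless something is added.

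A reader might infer that follow-up QoL will be inflated and the SD shrunk. The documents do not support that: they give no drop-out rate and no link with QoL, the bias is nil at an odds ratio of 1, and the SD can rise if loss falls in the mid-range. Nor does the trial exist to estimate this SD: acceptability and feasibility are primary, and QoL variability is one of several secondary outcomes. The article does not say which visit's SD will be used, and the baseline SD is untouched by later drop-out. A reader might also infer that the arms will differ because different people left; the figures above do not test that.

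A responder SD could be the right planning input, but only if the main trial repeats both the same available-case analysis and the same drop-out. Finally, a repeated-measures model implicitly continues QoL past death and corrects only part of the bias when drop-out depends on the unobserved current score. Both limits stand and belong in the fix.

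**Conclusion.** The point holds as a weak choice of method that is worth changing, not as a fatal flaw. The named tests leave collected data unused at exactly the visits where loss is likeliest. Under the assumed 30 to 32% loss by 24 weeks, OR 2.7 per SD and correlation 0.7, responder means are about 0.15 to 0.24 SD too high and SDs 3 to 7% too small. A main trial sized on such an SD would be about 6 to 13% short. The range starts at zero if drop-out is unrelated to QoL. The SD bias is smaller than the SD's sampling error, but it is systematic: a larger sample would not remove it, and under the plausible mechanism it points towards under-sizing.

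**What to change.** For the continuous QoL scores, replace the visit-by-visit t-tests and paired tests with one mixed model for repeated measures that includes baseline and all returned forms from every randomised participant, in the arm allocated. Then:

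- report model-based visit means, arm differences and SDs with 95% CIs beside the raw responder values;
- state which visit's SD, with its CI, goes into the main-trial calculation;
- report deaths separately;
- note that the model corrects only partly if drop-out depends on the current unobserved score.

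A table of baseline FACT-G, ECOG and age for those with and without 12- and 24-week forms is an optional supplement.

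The cost is a change of analysis wording, slightly more modelling work and possibly a slightly larger planned main trial. No new data are needed. In simulation at 30 per arm the model never gave a clearly worse SD or arm difference than the responder analysis.
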